#### Sacrospinous fixation

At least twenty procedures must have been performed by participating gynaecologists to eliminate a learning curve effect. All procedures are performed unilaterally to the right sacrospinous ligament. Access to sacrospinous ligament is obtained through the pararectal space. The posterior vaginal wall will be incised and separated from the rectum. The right ischial spine will be localised digitally and after retractor positioning the ligament is made visible through blunt dissection. Two permanent sutures (Prolene 1.0, Ethicon, Somerville, NJ, USA) will be placed through the right sacrospinous ligament at least 2 cm from the ischial spine. Hereafter, an additional anterior and/or posterior colporrhaphy or incontinence surgery can be performed. The permanent sutures will be placed through the posterior side of the cervix and two thirds of the posterior vaginal wall will be closed with absorbable sutures (Vicryl 2, Ethicon, Somerville, NJ, USA). The permanent sutures will be tightened and the cervix redressed. The remainder of the vaginal wall will be closed.

#### Vaginal hysterectomy

The patient is placed in lithotomy position and a tenaculum forceps is used to grasp the cervix. The vaginal wall around the cervix is circumcised. The bladder will be dissected and the anterior peritoneum opened. The posterior peritoneum will be opened and the Douglas cul-de-sac is entered. The uterosacral ligaments will be identified, transected and ligated. In several steps the uterus will be removed using clamps and sutures. Following removal of the uterus, the adnexa are inspected and the surgical pedicles are inspected for bleeding. The peritoneum is closed in a purse-string manner using a delayed-absorbable suture (Vicryl 1.0). The ligature of the uterosacral ligaments is sutured to the vaginal cuff to aid in long-term vaginal support. The vaginal wall incision is closed left to right with interrupted sutures.

During the same procedure additional anterior and/or posterior colporrhaphy or incontinence surgery can be performed.

### Statistical analysis

#### Sample size and power considerations

The sample size for this trial has been estimated using the hypothesis that both interventions are equivalent regarding anatomical outcome. The aim is to show that in the sacrospinous fixation arm, anatomical result is comparable to the vaginal hysterectomy group. Two groups of 94 patients will be included to yield a 80% power for a non-inferiority margin of 7%, assuming a relapse rate of 3% [18]. Considering a 10% loss in follow-up 104 women per arm are needed and thus a total of 208 women.

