**Methods/design:**

The SAVE U trial is a randomized controlled multi-center non-inferiority trial. The study compares sacrospinous fixation with vaginal hysterectomy in women with uterine prolapse stage 2 or higher. The primary outcome measure is recurrence of uterine prolapse defined as: uterine descent stage 2 or more assessed by pelvic organ prolapse quantification examination and prolapse complaints and/or redo surgery at 12 months follow-up. Secondary outcomes are subjective improvement in quality of life measured by generic (Short Form 36 and Euroqol 5D) and disease-specific (Urogenital Distress Inventory, Defecatory Distress Inventory and Incontinence Impact Questionnaire) quality of life instruments, complications following surgery, hospital stay, post-operative recovery and sexual functioning (Pelvic Organ Prolapse/Urinary Incontinence Sexual Questionnaire). Analysis will be performed according to the intention to treat principle. Based on comparable recurrence rates of 3% and considering an upper-limit of 7% to be non-inferior (beta 0.2 and one sided alpha 0.025), 104 patients are needed per group.

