### Randomisation

After patients have consented for participation in the study, they are randomized centrally through a website using computer-generated randomisation tables. The subjects are assigned in a 1:1 ratio to either sacrospinous fixation or vaginal hysterectomy. Randomisation will be stratified according to centre and severity of prolapse (POP-Q stage 2, 3 or 4). The details of the series are unknown to investigators or to the participating gynaecologists and all participants will receive unique study numbers.

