#### Data analysis

Patient characteristics will be summarized using descriptive statistics for continuous variables presented with medians, means and standard deviations as appropriate. Categorical data will be presented as rates and percentages. Anatomical outcome and recurrence rate assessed by a POP-Q-examination in both study groups will be considered as primary outcome. Surgical failure (recurrence) is defined as the presence of prolapse stage 2 or more in the middle compartment with prolapse complaints and/or redo surgery at one year follow-up. Non-inferiority of sacrospinous fixation to vaginal hysterectomy will be concluded if the lower limit of the 95% confidence interval lies above the non-inferiority margin of -7% (this is equivalent to performing a one-sided hypothesis test at the 0.025 level of significance, based on the null hypothesis that sacrospinous fixation is inferior to vaginal hysterectomy). If the 95% confidence interval for the difference in recurrence rates not only lies above the non-inferiority margin, but also above zero then it will be concluded that there is evidence of superiority of sacrospinous fixation over vaginal hysterectomy in terms of statistical significance at the 2-sided 5% level (p < 0.05).

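### At 94 women per arm, 80% power and a one-sided 2.5% error do not hold together: intervals that keep the error give about 63% power

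*Protocol article*

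**What the plan says.** Under Sample size and power considerations the protocol article states "Two groups of 94 patients will be included to yield a 80% power for a non-inferiority margin of 7" per cent, "assuming a relapse rate of 3" per cent. It then adds an allowance for attrition: "Considering a 10% loss in follow-up 104 women per arm are needed and thus a total of 208 women".

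The Abstract (Methods/design) gives the same design: "Based on comparable recurrence rates of 3" per cent and "considering an upper-limit of 7% to be non-inferior (beta 0.2 and one sided alpha 0.025), 104 patients are needed per group".

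Under Data analysis, non-inferiority is judged by comparing one limit of a 95% confidence interval for the difference in recurrence with the 7-point margin. Of this rule the article says "this is equivalent to performing a one-sided hypothesis test at the 0.025 level of significance".

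The article names neither the sample-size formula nor the type of confidence interval.

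**The concern.** The plan claims two properties at once for 94 evaluable women per arm: an 80% chance of showing non-inferiority when both operations have 3% recurrence, and at most a 2.5% chance of accepting sacrospinous fixation when it is worse by the full margin. At 3%, the expected number of failures is 94 × 0.03 = 2.82 per arm. A normal approximation to a difference of two proportions is unreliable with so few events, so both properties need an exact check.

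If they cannot both hold, one of two things follows, depending on the interval used. Either the trial runs a materially larger risk of accepting an inferior operation than it states, or it is much more likely than stated to end without a conclusion. Two analysts could also reach opposite primary conclusions from the same small counts. The Background reports 27% versus 3% recurrence, to the disadvantage of sacrospinous fixation, in the one earlier randomised trial, so a false claim of non-inferiority is the error to guard against most.

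**Working it through.** **Inputs**

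- Recurrence 3% in both arms, margin 7 percentage points, power 80%, 94 evaluable per arm, 104 per arm after 10% loss (Sample size and power considerations).
- One-sided alpha 0.025 (Abstract; repeated under Data analysis).
- Allocation 1:1 (Randomisation).

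**Step 1: reproduce the plan's figure.** The unpooled normal formula gives

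n = (1.96 + 0.8416)² × 2 × 0.03 × 0.97 / 0.07² = 93.2, rounded up to 94 per arm.

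The same formula puts power at 80.3% for n = 94. The allowance for loss is 94 × 1.1 = 103.4, rounded up to 104. A one-sided alpha of 0.05 would give 74 and an equivalence design 125, so neither explains 94. The plan's number is therefore reproduced.

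**Step 2: exact properties at 94 per arm.** Let d be recurrence after sacrospinous fixation minus recurrence after hysterectomy. Non-inferiority is declared when the upper 95% limit for d is below +7 points, which is the plan's rule with the sign reversed. For each pair of failure counts (a, b), determine whether the rule passes, then sum over all passing pairs

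Bin(a; 94, p₁) × Bin(b; 94, p₂).

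Power takes p₁ = p₂ = 0.03. The type I error takes p₁ = p₂ + 0.07.

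| Interval | Power, 3% v 3% | Error, 10% v 3% | Error, 8% v 1% | Error, 7% v 0% |
|---|---|---|---|---|
| Wald | 79.0% | 3.8% | 5.7% | 9.8% |
| Miettinen-Nurminen | 62.6% | 2.0% | 1.5% | 0.9% |
| Newcombe | 62.6% | 2.0% | 1.5% | 0.9% |

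Other methods at n = 94 (power; error at 10% v 3%):

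- Farrington-Manning: 62.6%; 2.0%.
- Unconditional exact test on the score statistic, calibrated to size at most 0.025 along the whole boundary: 62.6%; 2.0%.
- Wald with continuity correction: 69.3%; 2.1% (rising to 3.6% as the hysterectomy rate approaches 0).
- Newcombe with continuity correction: 55.7%; 1.3%.
- Agresti-Caffo: 74.0%; 2.9%.

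No method combines 80% power with an error of 2.5% or less.

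**Step 3: does the 10% allowance rescue it?** With all 104 per arm evaluable, power is 71.2% (Miettinen-Nurminen) or 71.5% (Newcombe). Wald gives 81.3%, with error still 3.4% at 10% v 3%.

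**Step 4: size needed for 80%.** Newcombe first reaches 80% at 123 per arm and Miettinen-Nurminen at 125 (80.3%). Because counts are discrete, power then dips slightly below 80% (79.7% at 128 for both). It is 80.8% (Miettinen-Nurminen) and 82.9% (Newcombe) at 130, and above 80% at the larger sizes tried. A fair summary is 125 to 130 evaluable per arm; 125 / 0.9 = 138.9, so about 139 randomised per arm.

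**Step 5: effect on the verdict.** Take 3/94 failures after sacrospinous fixation and 1/94 after hysterectomy.

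- d = 0.0319 − 0.0106 = 0.0213.
- Wald standard error = √(0.0319 × 0.9681/94 + 0.0106 × 0.9894/94) = 0.0210.
- Wald upper limit = 0.0213 + 1.96 × 0.0210 = 6.2%: passes.
- Miettinen-Nurminen upper limit = 8.1%: fails. Newcombe = 8.0%: fails.

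The results 2 v 0, 3 v 2 and 4 v 3 split in the same way. Under 3% in both arms, Wald and Miettinen-Nurminen disagree in 16.4% of trials, and in every one of them it is Wald that declares non-inferiority.

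**The case against.** Several points can fairly be made for the plan.

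- **There is no slip in the arithmetic.** The 94 follows from a standard non-inferiority formula. This stands. The fault is in relying on that formula at about three events per arm. Its use is also inferred from the match, not stated.
- **The interval method may be fixed in an analysis plan that is not shown, and nothing says Wald will be used.** This also stands: the inflated error arises only under Wald. It does not save the plan, because the protocol itself states the combination of 80% power and 0.025. If the analysis plan names Wald, the 0.025 is wrong; if it names a score-type or exact method, the 80% is wrong.
- **The larger error figures lie away from the design assumption.** The 9.8% needs a hysterectomy recurrence of 0% and the 5.7% needs 1%. At the planned 3% the Wald error is 3.8%, an excess of 1.3 points, about half as much again as claimed. That is the figure to lead with.
- **The verdict usually does not depend on the method.** In about 84% of trials at 3% in both arms, Wald and Miettinen-Nurminen agree. A one-in-six dependence on an unnamed method is still too much for a primary conclusion.
- **The 63% is specific to score and Newcombe intervals.** Methods within 0.025 at 10% v 3% span about 56% to 69%. None approaches 80%.
- **With a score interval the consequence is an inconclusive trial, not a false claim.** True, but readers and sponsor would then have been told 80% where the chance is about 63%.

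**Conclusion.** The concern holds. At 94 evaluable women per arm, the stated 80% power and one-sided 0.025 error are not both attainable with any interval or test examined. Keeping the error gives about 63% power (71 to 72% with all 104 evaluable). Obtaining about 80% requires the Wald interval, whose one-sided error is 3.8% at the planned hysterectomy rate and higher if that rate is lower.

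The power figures rest on the plan's own assumption of 3% in both arms, independent binomial counts and an unstratified risk difference. The uncorrected score and Newcombe intervals stay within 2.5% for hysterectomy recurrence up to 10% (maximum 2.3%). They reach 2.8% only near 46%, which is irrelevant here.

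The interval can reverse the primary conclusion on plausible counts, so this must be settled before outcome data are examined.

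**What to change.** Under Data analysis, name the Miettinen-Nurminen (or Newcombe) two-sided 95% confidence interval for the risk difference as the primary interval. Choose one of the two and state that the Wald interval will not be used. If an analysis plan already names a method, the protocol and that plan should agree.

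Under Sample size and power considerations, and in the Abstract, replace the 80% with the power that goes with that interval: about 63% with 94 evaluable per arm and about 71% if all 104 are evaluable, assuming 3% recurrence in both arms.

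The cost is a sentence or two and a less favourable stated power; no extra patients are required. If the sponsor wishes to keep 80% power, the target is about 125 to 130 evaluable per arm (about 139 randomised per arm for 125 evaluable), which is a separate decision.

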#### Data analysis

Patient characteristics will be summarized using descriptive statistics for continuous variables presented with medians, means and standard deviations as appropriate. Categorical data will be presented as rates and percentages. Anatomical outcome and recurrence rate assessed by a POP-Q-examination in both study groups will be considered as primary outcome. Surgical failure (recurrence) is defined as the presence of prolapse stage 2 or more in the middle compartment with prolapse complaints and/or redo surgery at one year follow-up. Non-inferiority of sacrospinous fixation to vaginal hysterectomy will be concluded if the lower limit of the 95% confidence interval lies above the non-inferiority margin of -7% (this is equivalent to performing a one-sided hypothesis test at the 0.025 level of significance, based on the null hypothesis that sacrospinous fixation is inferior to vaginal hysterectomy). If the 95% confidence interval for the difference in recurrence rates not only lies above the non-inferiority margin, but also above zero then it will be concluded that there is evidence of superiority of sacrospinous fixation over vaginal hysterectomy in terms of statistical significance at the 2-sided 5% level (p < 0.05).

### Ethics

The study is conducted in accordance with the principles of the Declaration of Helsinki and 'good clinical practice' guidelines. The SAVE U trial has been approved by the Medical Ethical Committee of the Isala Klinieken Zwolle (MEC 09/625) and the local Ethical Committees of the participating centers. Prior to randomization informed consent will be obtained.

## Discussion

This is a protocol for a randomised trial comparing sacrospinous fixation and vaginal hysterectomy for the treatment of uterine prolapse POP-Q stage 2 or higher with regard to anatomical outcome, post-operative recovery, length of hospital stay, complications and sexual functioning.

The findings of this trial will contribute to answer the question which surgical treatment is preferable in women with symptomatic uterine prolapse POP-Q stage 2 or higher. If equivalence in anatomical outcome is found, the comparison of the secondary outcomes will be essential in selecting the preferred strategy.
